### Compliance

EMA compliance rates will be based on answered surveys divided by the total number of scheduled EMA surveys for each participant. We will also monitor participation rate, missing data, latency period (defined as the time between receiving EMA prompts and the items answered), and attrition rate [38]. In additionally, we will follow up each participant daily, irrespective of the compliance rate, to ensure that they do not have issues with device use. Basic statistical analyses will be performed to better understand participant compliance, such as compliance rate, missingness, participation rate, and latency period. In addition, as an exploratory analysis, the missingness of EMA surveys will be examined using pattern mixture random-effects modeling [39]. Furthermore, mindless EMA responses to surveys may occur. To address this issue, we have selected survey items that are crucial to our study aims to minimize participants’ burden.

### Preliminary Study

Before this pilot study, we conducted the DC CV Health and Needs Assessment (DC-CHNA) study (NCT019227783) to investigate bio-psychosocial and neighborhood conditions resulting in poor CV health. The objective of the previous work was to determine ways to use mobile health technology to promote CV health for populations in lower SES DC Wards 5, 7, and 8 [40-44]. First, the DC-CHNA created a community advisory board, the DC Cardiovascular Health and Obesity Collaborative (DC-CHOC), to give feedback on developing and implementing the DC-CHNA and subsequent community-based projects. The DC-CHOC consists of representatives from the DC faith-based community, US government agencies, academia, and health advocacy organizations, all of whom are devoted to addressing obesity and CV health in at-risk DC communities [44-47]. In this study, 11 participants from DC-CHNA were asked to carry GPS units and use the EMA app and then test the feasibility of both a GPS device and an EMA app for African American women.

### Schedule of Events

Participants will visit the NIH Clinical Center where we will instruct them on how to use the devices and measurement tools (accelerometer, GPS, and EMA; Table 1). During the inpatient visit, we will conduct a cardiovascular examination, draw blood, and conduct a vascular stiffness test. Participants will also undergo 18F-FDG-PET/CT testing to measure chronic stress–related neural activity (ie, amygdala brain activity) and vascular inflammation. On the first day of the inpatient visit, study volunteers will follow a controlled eucaloric diet containing 55% carbohydrate, 15% protein, and 30% fat and providing 150% of their estimated resting energy needs in preparation for testing to accurately measure energy expenditure on inpatient day 2. Resting energy expenditure has not been included in the aims of this study. However, this measure can be evaluated as a moderator for the sub-aims of aims 1 and 2.

**Table 1 table1:** Schedule of events.

Events				First Clinical Center visit					At least 14-day monitoring			2nd Clinical Center visit
				Day 1		Day 2						
Recruitment				Ongoing		Ongoing		Ongoing			Ongoing	
Informed consent				✓								
Vital signs				✓								
Anthropometric measures				✓								
Clinical blood testing				✓							✓	
Cardiovascular examination				✓							✓	
Blood pressure				✓							✓	
Blood glucose				✓							✓	
Hemoglobin A_1c_				✓							✓	
Lipid panel				✓							✓	
Resting energy expenditure						✓						
18-fluorodeoxyglucose positron emission tomography-computed tomography						✓						
Pulse wave velocity				✓								
**Survey assessments^a^**												
	Sociodemographic characteristics			✓							✓	
	Medical history			✓							✓	
	**Health behaviors**			✓							✓	
		Self-rated health	✓							✓		
		Smoking status	✓							✓		
		Alcohol use	✓							✓		
		General physical activity level	✓							✓		
		Illicit drug use	✓							✓		
		Sleep duration and quality	✓							✓		
		Dietary intake	✓							✓		
	Perceived Stress Scale			✓							✓	
	Center for Epidemiological Studies-Depression Scale			✓							✓	
	Hamilton Anxiety Rating Scale			✓							✓	
	Adverse Childhood Experiences			✓							✓	
	Life Orientation Test-Revised (a measure of optimism)			✓							✓	
	MacArthur Scale of Subjective Social Status			✓							✓	
	Perceived Ethnic Discrimination Questionnaire Community Version			✓							✓	
	Positive and Negative Affect Schedule			✓							✓	
	Superwoman Schema			✓								
	Perceived Neighborhood Environment			✓							✓	
	COVID-19 surveys			✓								
**Physical activity, sedentary behavior, sleep, and neighborhood disorder assessments**												
	Physical activity and sedentary behavior via accelerometers							✓				
	Sleep duration via accelerometers							✓				
	GPS monitoring							✓				
	Ecological momentary assessment							✓				
	Engagement with the DC Cardiovascular Health and Obesity Collaborative Community Advisory Board			Ongoing		Ongoing		Ongoing			Ongoing	

^a^The surveys can be completed at the first or second clinical visit and will not be repeated.

During their baseline visit, participants will also undergo anthropometric measurements, including height, weight, waist circumference, and hip circumference for weight-related outcomes; complete questionnaires to measure demographics and medical history, health behaviors (eg, PA [48]), perceived neighborhood measures, psychosocial factors (eg, perceived general stress [49]), and COVID-19 questionnaires [50,51]. The majority of the participants will complete the survey questionnaires during the baseline visit (visit 1). For some reason, if participants do not complete the surveys during visit 1, we allow them to complete surveys during the 2nd visit to avoid protocol deviation. A second blood draw will be performed within 14 days from the first draw, as a second baseline to account for the variability of sensitive biological measures. This study follows a tiered compensation format where total compensation depends on the number of assessments the participant completes.

After the baseline assessment (ie, clinical visit days 1 and 2), participants will wear an accelerometer to objectively measure PA and carry a GPS unit to assess locations where they engage in PA for at least a 14-day period [52]. Concurrently, participants will carry a smartphone to receive EMA surveys that have been previously validated to measure psychosocial factors, including mood and stress, for a 14-day period. Subsequently, we will create GIS-derived neighborhood environmental variables, psychosocial variables (EMA), PA or sedentary behavior, and diet outcomes using data from the surveys, EMA, accelerometers, and GIS unit. We will then examine associations between environmental exposures and biological measures, psychosocial factors, PA or sedentary behavior, and dietary intake.

### Measures

#### Outcomes

Participants will visit the NIH Clinical Center for 18-FDG PET/CT to measure stress-related neural activity. In brief, we will assess amygdala uptake as published [19,53]. Immune activation testing from collected blood will be performed within the NIH Clinical Center.

Two measures of vascular inflammation and function will be used (Table 2). First, the target-to-background ratio for aortic vascular inflammation will be measured through the whole body FDG PET/CT to examine amygdala activity [54]. Second, the pulse wave velocity and augmentation index as a measure of large-vessel vascular function will be determined by the Sphygmocor system (AtCor Medical), a noninvasive tool [55]. The noninvasive measure of vascular function has been validated and used widely.

**Table 2 table2:** Biological measures, physical activity, residential and GPS activity space, and ecological momentary assessment measures.

Measures			Description
**Outcomes**			
	Stress-related neural activity	Amygdala activity (18F-FDG^a^ PET/CT^b^)	
	Vascular inflammation and function testing	Vascular inflammation: arterial Inflammation (18F-FDG PET/CT) Vascular function: pulse wave velocity and augmentation index (Sphygmocor)	
	Immune system activation	Flow cytometry-based characterization of immune cell populations and their receptor expression profile (two flow cytometry panels) [56]: (1) CD3, CD14, CD15, CD16, CD19, CD42b, CD45, CD56, CD203c, and CD193 and (2) CD3, CD14, CD16, CD56, CD98 heavy chain, CD64, CCR2^c^, CCR5, and TLR2^d^	
	Immune cell function	Natural killer cell function profiling by detecting degranulation and cytolytic activity [57,58] Monocyte function profiling [59], including ability of monocytes to perform chemotaxis and migration, as well as determination of inflammasome activity	
	Biomarker-based immune system activation	Cytokine and chemokine profiling [60] eg, TNF-α^e^, IL-6f, IL-10, IL-8, IL-1β, IFN-α^g^, IFN-γ, MCP-1^h^, VEGF-A^i^, IL-RA^j^, IL-18, TGF-β^k^ Stress-induced neurotransmitter profiling, including epinephrine, norepinephrine, dopamine, and cortisol [61]	
**Exposures**			
	Residential and GPS activity space (model: BT-Q1000XT)	Neighborhood Deprivation Index [62,63] based on US census [62], social disorder based on virtual neighborhood audits [41,64], crime rate around GPS activity space based on police crime report [65], and modified retail food environment index. All measures will be created based on GPS activity space [66] Count and density of parks, gyms, and recreation facilities [67] around GPS activity space	
**Moderators**			
	PA^l^ via accelerometer or survey	A minute-by-minute PA (A^m^), daily mean moderate-to-vigorous PA minutes (A), total PA minutes (A), active transportation PA, and leisure-time PA minutes [46] (S^n^)	
	Psychosocial factors via ecological momentary assessment	Perceived neighborhood social environment [68,69]; mood states [70], perceived stress [49], and daily hassles [71]	

^a^FDG: fluorodeoxyglucose.

^b^PET/CT: positron emission tomography-computed tomography.

^c^CCR2: C-C chemokine receptor type 2.

^d^TLR2: toll like receptor 2.

^e^TNF-α: tumor necrosis factor α

^f^IL-6: interleukin-6.

^g^IFN-α: interferon-α.

^h^MCP-1: monocyte chemoattractant protein-1.

^i^VEGF-A: vascular endothelia growth factor-A.

^j^IL-RA: receptor antagonist.

^k^TGF-β: transforming growth factor β.

^l^PA: physical activity.

^m^A: assessed by accelerometer.

^n^S: assessed by survey.

The outcomes for immune cell activation studies will be the proportion of each detected immune cell, their receptor expression, and platelet adhesion (eg, proportion of classical clusters of differentiation, such as CD14+CD16- monocytes of all monocytes, or proportion of natural killer cells of all CD45+ cells; Table 2). Immune cell function for purified and isolated monocytes and natural killer cells will also be determined for each participant. For instance, the ability of monocytes to perform chemotaxis, migrate toward the monocyte chemoattractant protein-1 gradient, will be determined based on a chemotaxis coefficient, as well as the activity of the inflammasome by measurement of interleukin (IL)-1β and IL-18 release by enzyme-linked immunosorbent assay upon appropriate stimulation. In biomarker profiling, plasma or serum levels of the proposed cytokines, chemokines, and stress-related neurotransmitters, and hormones will be measured as concentrations in pg/mL.

#### Exposures

Two distinct types of neighborhood exposures will be created (Table 2): (1) residential neighborhood variables around participants’ homes [25-27] and (2) GPS activity space (ie, places where participants travel throughout the day) [25-27]. Each type of measure will be linked to accelerometer data with respective time and measured intensity of PA levels (Figure 2; Table 2). Both residential and GPS activity space measures will include neighborhood poverty (eg, neighborhood deprivation index from US census [62,63]), physical disorder (by virtual neighborhood audits [41,64]), police-reported crime (from DC databases [65,72]), and the modified retail food environment index (defined as the ratio of healthy to unhealthy food stores) [73]. In addition, parks, gyms, and recreation facilities will be used to create the count and density of these PA facilities to better understand how participants engage in PA [67]. As a measure of feasibility and practicality, we used 11 participants from a protocol (ClinicalTrials.gov identifier NCT03288207) to create residential buffers around participants’ homes (ie, circular [25-27] and line-based road network buffers; Figure 3 [74]) and GPS activity space buffers based on SD ellipses [66,75] (Figure 4) and individuals’ daily paths (Figure 5) [66]. Figures 2-5 were based on hypothetical data to show each different buffer and buffer type (actual study participant data are not shown). Some points occurring around residential areas will be weighted.

**Figure 2 figure2:**
[figure not shown]
Minute-by-minute accelerometer data linked to GPS coordinates. Note: each point represents a minute of physical activity, ranging from sedentary to vigorous intensity levels.

**Figure 3 figure3:**
[figure not shown]
Residential buffers around participants’ home based on circular and line-based road network buffers.

**Figure 4 figure4:**
[figure not shown]
GPS activity space buffers based on SD ellipses.

**Figure 5 figure5:**
[figure not shown]
GPS activity space buffers based on individuals’ daily paths.

In Table 3, real-time EMA measures will include perceived neighborhood social environment (eg, violence and safety), mood states (positive or negative affect [70]), perceived stress (eg, stressed and irritated [49]), and daily hassles (eg, work load [71]) with three random prompts within defined timeframes (7-9 AM, 11 AM-1 PM, and 5-7 PM) throughout the day (Table 3; Figure 6) [36]. Participants will initiate their own EMA recording when they start engaging in a certain activity (ie, event contingency; Table 3; Figure 6) [68,69]. The event contingency approach is based on a self-initiated response to behaviors and contexts. Participants will be instructed on how to initiate the EMA recording and respond to a certain activity and when to initiate their EMA recording. For example, when participants commute to work by car, they initiate it by themselves and record their mode of activity in the smartphone app. EMA measures will be merged with GPS activity space measures with the respective timestamps. Before the full pilot study, we tested GPS units and EMA using a smartphone app (ilumivu, Inc) to identify any potential barriers to use.

**Table 3 table3:** Random prompts and event contingency items for ecological momentary assessment.

Variable			Item		Response options

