**Items for random prompts**					
	Positive and negative affect [70]	“Since the last EMA^a^ signal, how much of the time did you feel...?” Cheerful In good spirits Extremely happy Calm and peaceful Satisfied Full of life So sad Nervous Restless or fidgety Hopeless Worthless Everything was an effort		Very slightly or not at all A little Moderately Quite a bit Extremely	
	Perceived stress scale [49]	“How certain do you feel that you can deal with all the things that you have to do right now?”		Not at all A little Quite a bit Extremely	
	Perceived stress scale [49]	“How confident do you feel about your ability to handle all of the demands on you right now?”		Not at all A little Quite a bit Extremely	
	Daily hassles [71]	“Have you experienced a stressful event since your last entry?”		Yes or no	
	Daily hassles [71]	“Have you experienced a stressful or problematic social interaction since last entry?”		Yes or no	

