**Items for event contingency** **[68,69]**					
	Physical activity behavior	“What type of physical activity/exercise are you doing?”		Walking Running or jogging Weightlifting or strength training Using cardiovascular equipment Bicycling Other (write in)	
	Physical context	“WHERE are you?”		Home (indoors) Home (outdoor) Work (indoor) Outdoors (not at home) Car, van, or truck Other (write in)	
	Physical context	“WHERE are you AT HOME?” (Indoors)		Bedroom Family or living room Kitchen Garage Other (write in)	
	Physical context	“WHERE are you AT HOME?” (Outdoors)		Pool Deck, patio, or balcony Yard Driveway Other (write in)	
	Physical context	“Where are you OUTDOORS?” (Outdoors not at home)		Park or trail Road Sidewalk Parking lot Other (write in)	
	Vegetation	“How many TREES AND PLANTS are there in the area where you are right now?”		No trees or plants A few trees and plants Some trees and plants A lot of trees and plants	
	Traffic	“How much TRAFFIC is on the closest street to where you are right now?”		No traffic A little traffic Some traffic A lot of traffic	
	Litter	“How much LITTER or GARBAGE is on the ground where you are right now?”		No litter A little litter Some litter A lot of litter	
	Safety	“Do you feel safe in your current location?”		Yes or no	
	Safety	“Is violence a problem in your current location?”		Yes or no	

^a^EMA: ecological momentary assessment.

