### Merging Multiple Data

Complete master data will be created based on multiple data sources, including PA via accelerometers (ie, 1-minute epochs), GPS units (1-minute epochs), and EMA via a smartphone app (3 times/day). First, each recording of the GPS points will be linked to the respective time-stamped accelerometer data for each minute. Then, EMA data (three times through morning, afternoon, and evening assessments) will be linked to the corresponding GPS and accelerometer data. The complete data will then be collapsed by hours, time of day (morning, afternoon, and evening), and days.

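### The text places the EMA safety and violence items at the random prompts, but Table 3 places them only in self-initiated event recordings; the two must be reconciled before this EMA exposure can be analysed

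*Protocol article*

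**What the plan says.** The Exposures section introduces Table 3 by stating that "real-time EMA measures will include perceived neighborhood social environment (eg, violence and safety"), together with mood, stress and hassles, will be collected "with three random prompts within defined timeframes (7-9 AM, 11 AM-1 PM, and 5-7 PM) throughout the day". The Devices section lists safety and violence as survey content immediately after describing the random prompts.

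Table 3 splits the items differently. The block headed "Items for random prompts" holds affect, two perceived-stress items and two daily-hassles items, ending with "Have you experienced a stressful or problematic social interaction since last entry". The safety items, "Do you feel safe in your current location" and "Is violence a problem in your current location", are in the event-contingency block with litter, traffic, vegetation and location.

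Merging Multiple Data says that "EMA data (three times through morning, afternoon, and evening assessments) will be linked to the corresponding GPS and accelerometer data"; it does not mention event records.

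Statistical Analysis relates neighborhood variables from residential, GPS and EMA sources, separately, to the outcomes of aims 1, 2 and 3. Physical activity is a covariate throughout and a tested moderator in sub-aims 1 and 2. Table 2, under Moderators, lists for EMA "Perceived neighborhood social environment [68,69]; mood states [70], perceived stress [49], and daily hassles [71". The Devices section names only mood and stressors as the psychosocial factors for the sub-aims.

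**The concern.** The text and the item table give two different measurement schemes for the same exposure. Under one, every woman is asked about safety at times she does not choose. Under the other, she is asked only when she opens a recording herself.

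Under the second scheme, whether a woman has the exposure at all, and how many answers it averages, depends on how often she logs events. The named trigger is physical activity, and the first event item asks which exercise is under way. Noise in a person-level mean pulls its association with the outcome toward zero. If less active women log less, their slope is pulled further, which can imitate or hide the interaction with physical activity that sub-aims 1 and 2 test. This does not require women to avoid unsafe places. An item that was never asked cannot be recovered afterwards.

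**Working it through.** The plan gives no figure to reproduce here, so the first step is to set the sections side by side.

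| Place | When safety and violence are asked |
|---|---|
| Devices | Listed as survey content right after the random prompts; not limited to events |
| Exposures, text before Table 3 | At three random prompts a day |
| Table 3, random-prompt block | Not listed |
| Table 3, event-contingency block | Listed |
| Merging Multiple Data | EMA enters as three assessments a day; events not mentioned |

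The citations side with Table 3. Table 2 attaches references 68 and 69 to the perceived neighborhood measure, and the same two references label the event-contingency block and the sentence on self-initiated recording. The random-prompt items carry 70, 49 and 71.

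Reading Table 3 and the merge section together, a file built from the three daily assessments contains no safety or violence answers. If event records are added, it contains only self-initiated ones.

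The rest shows scale only. The documents supply three prompts a day (Exposures), a maximum of nine (Devices), 14 days of EMA and 60 women. The number of events per woman is not given and is assumed.

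- **Scheduled answers if asked at prompts:** 3 × 14 = 42 per woman, or up to 9 × 14 = 126, whatever her activity.
- **Women with no data if asked at events only** (Poisson count with mean m, 60 × exp(−m)): m = 1 gives 60 × 0.368 = 22.1; m = 2 gives 60 × 0.135 = 8.1; m = 3 gives 60 × 0.050 = 3.0; m = 7 gives 0.1.
- **Standard error of one woman's share of unsafe reports** (√(p(1−p)/n), assumed p = 0.20): n = 2 gives 0.283; n = 7 gives 0.151; n = 14 gives 0.107; n = 42, which assumes every prompt is answered, gives 0.062.
- **Direction of any shift**, if 10% of time is activity, events are logged only then, and the unsafe share is 0.20 otherwise (all assumed): with 0.05 during activity, the all-day share is 0.1 × 0.05 + 0.9 × 0.20 = 0.185 and events read 0.05. With 0.30 during activity, it is 0.1 × 0.30 + 0.9 × 0.20 = 0.21 and events read 0.30. With 0.20 in both, there is no shift.

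**The case against.** The strongest reply is that the text already says what is wanted. Exposures and Devices point to the random prompts, so Table 3 may simply be mislabeled, and Figure 6, which is not shown here, may settle it. That stands as a reason not to treat event-only collection as fact. It does not remove the contradiction, since Table 3 is the only place where the items are assigned.

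A reader might infer that the exposure is observed only while a woman exercises, and so is selected on the moderator. The documents do not support that. A car commute is a worked example of an event, the location options include indoor rooms, work and vehicles, and the moderator is accelerometer-measured activity rather than logging. The link to activity is probable, not stated.

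A reader might also infer a bias toward safe answers. Nothing in the protocol supports a direction, and the arithmetic allows either direction or none.

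The Exposures text also says that EMA measures will be merged with GPS measures by timestamp, without limiting this to prompts, so event records may reach the file. That is why the consequence is stated as absent or self-selected.

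Two further inferences fail. No section has a variable moderating itself, since perceived environment could moderate a residential or GPS exposure. The compliance rate is defined for scheduled surveys, so having no denominator for events is not a defect.

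Finally, this is a pilot, and Table 1 also schedules a perceived neighborhood survey. Both limit the damage.

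**Conclusion.** The contradiction is firm and rests on the text alone. Its consequence is conditional: if Table 3 is implemented, the EMA neighborhood exposure in aims 1 to 3 is missing from the merged file or observed only at self-chosen events, and its availability and precision probably vary with activity. The size ranges from negligible (about 7 or more events per woman) to roughly a third of the sample without data (an average of one, 22 of 60), under an assumed Poisson count. The direction of any bias is unknown.

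Only the EMA version of the exposure is touched; the ward comparison and the residential and GPS exposures stand. The role of EMA perceived environment is also inconsistent: moderator in Table 2, exposure in Statistical Analysis, and not among the sub-aim factors in Devices. That is a smaller matter of wording, but it should be settled at the same time.

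**What to change.** Align Table 3 with the Devices, Exposures and Merging Multiple Data sections:

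- Add the two yes/no items (feeling safe; violence a problem) and the one location item to the random prompts.
- Build the person-level EMA neighborhood exposure from prompt answers only.
- Keep event records as descriptive context, and report their number by level of physical activity.
- In Table 2, move the EMA perceived neighborhood environment to Exposures and leave mood, stress and hassles as the EMA moderators, so that it agrees with Statistical Analysis and Devices.

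If the prompts cannot be changed, correct the Exposures text, define the variable as perceived environment during recorded events, state how event records enter the merge, and still report their number by activity level.

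The cost is reprogramming the app and slightly longer prompts. Table 3 now has 12 affect, 2 stress and 2 hassles items, so a prompt would go from 16 to 19 short items. That is some added burden, which the Compliance section aims to keep low. The article places recruitment in the future, so as written the change could still be made before data collection.
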